## Abstract

**Introduction:**

Sarcomas are rare tumours with considerable heterogeneity. Early and accurate diagnosis is important to optimise patient outcomes in terms of local disease control, overall survival (OS) and health-related quality of life (HRQoL). Time to diagnosis is variable in bone as well as soft tissue sarcoma. Possible factors for a long time from first symptom to diagnosis (the total interval) include patient, tumour and healthcare characteristics, but until now the most relevant risk factors and its association with outcomes remain unknown. Our study aims to (1) quantify total interval, the time interval from first symptom until (histological) diagnosis; (2) identify factors associated with interval length and (3) determine the association between total interval and HRQoL, stage and tumour size at diagnosis, progression-free survival (PFS) and OS.

**Methods and analysis:**

We will conduct a longitudinal, prospective, international, multicentre cohort study among patients aged ≥18 years with newly diagnosed bone or soft tissue sarcoma at eight centres (three in UK, five in The Netherlands). Patients will be asked to complete questionnaires at five points in time; one at diagnosis and at follow-up points of 3, 6, 12 and 24 months. Questionnaire data is collected within the Patient Reported Outcomes Following Initial treatment and Long term Evaluation of Survivorship (PROFILES) registry: an international data management system for collection of patient-reported outcomes. Clinical data will be extracted from patient records. The primary endpoint is HRQoL at diagnosis, measured with the EORTC QLQ-C30. Secondary endpoints are stage and tumour size at diagnosis, PFS, OS, additional patient-reported outcomes, such as quality-adjusted life years and psychological distress.

**Ethics and dissemination:**

Ethical approval was given by the Health Research Authority and Research Ethics Committee for the United Kingdom (18/WA/0096) and medical ethical committee of Radboudumc for The Netherlands (2017-3881). Results will be presented in peer-reviewed journals and presented at meetings.

**Trial registration number:**

NCT03441906.

Strengths and limitations of this studyThe international design allows for comparison of healthcare systems and its influence on total interval length.Multicentre, prospective design allows reliable comparison of sarcoma subgroups to make clinically relevant recommendations to improve total interval.Inclusion of patients at diagnosis minimises recall bias for total interval length.Patients were actively involved in the design of this study and mentioned earlier diagnosis and patient-reported outcomes as research priorities.

## Introduction

Sarcomas are a group of solid mesenchymal tumours, which comprise more than 70 histological subtypes, with considerable heterogeneity with respect to age at diagnosis, location, biological behaviour and outcome.^1^ Approximately 80% of sarcomas are soft tissue sarcomas (STS), the remainder are bone sarcomas. Sarcomas are typical examples of so-called rare cancers, with an estimated European incidence of 4–5 per 100 000 per year when taken all together,^2^ accounting for 1% of adult solid malignant cancers.^3^ Patients with rare cancers have a higher mortality rate than those with common cancers, due to delays in diagnosis, suboptimal or inadequate treatment, fewer developments in novel therapies and opportunities to participate in clinical trials.^4^

Early and accurate diagnosis of cancer is important to optimise patient outcomes in terms of local disease control, overall survival (OS) and health-related quality of life (HRQoL).^5 6^ However, because of the heterogeneity and rarity of sarcomas, there is a lack of public awareness, limited experience of primary and secondary healthcare professionals and absence of a typical presentation, resulting in late referrals to specialist sarcoma centres and prolonged time to diagnosis.^7^

Time to diagnosis can be defined according to the research framework from Olesen *et al,*^8^ which we adapted to the situation as applicable for sarcomas.^9 10^ The time between first symptom and (histological) diagnosis is known as the total interval. This includes a patient and diagnostic interval, defined as time between onset of symptoms until consultation of a healthcare professional and time between consultation of a healthcare professional and diagnosis, respectively. The latter can be further divided into a primary, secondary and tertiary care interval, each of which refers to first consultation until referral to the next caregiver or diagnosis.

Possible risk factors for a prolonged total interval could be patient, tumour or healthcare system characteristics. In order to study the latter, it is informative to compare patients from different countries. In both the Netherlands and UK, general practitioners (GPs) have an important role as healthcare gatekeepers. In general, people consult their GP who then decides whether referral is warranted and determines the acuteness and location of the referral. In the UK, privately insured patients can also self-refer to a hospital without seeing a GP. Furthermore, within the UK, a considerable amount of patients with cancer is diagnosed at an emergency department, associated with worse outcomes.^11^ Sarcoma care is formally centralised within the UK, whereas the Netherlands has bone sarcoma centres, and referral to dedicated STS centres is encouraged, but not commissioned. Furthermore, cultural differences may play a role in patient behaviour. Also, longer travel time to a sarcoma centre in the UK compared with the Netherlands may also affect total interval length.

Up to now, only few studies regarding total interval length and clinical outcomes in sarcoma have been published, most were retrospective and included mainly children. Some studies found that a longer total interval worsened OS, while others did not find inferior clinical outcomes.^10^ Researchers have argued that this lack of an association, often referred to as the ‘waiting-time paradox’, may be because the studies have not been able to adequately adjust for the aggressiveness of the cancer tumours. The most significant effect of a long interval for sarcomas seems to be the increasing size of the lesion,^12^ with consequent decreased chance of uncomplicated resection with clear surgical margins, a greater risk of amputation and increased risk of developing metastases.^13^ This may also affect patient-reported outcomes such as HRQoL of patients with sarcoma.

HRQoL is the patients’ perception of his overall health in relation to physical, psychological and social aspects in life.^14^ Three systematic reviews have been published on HRQoL of patients with sarcoma, however, none of these looked at the association of total interval length and HRQoL.^15–17^ In other cancers and chronic diseases, lengthening of total interval was associated with decreased HRQoL.^18 19^ HRQoL is an interesting outcome parameter for evaluating consequences of long total interval length and provides an insight into the patient’s experience of the consequences of diagnostic delay. In addition to using patient-reported outcomes as a measure for quality of care, HRQoL can be used to conduct cost-utility analysis to estimate the ratio between the cost of a prolonged total interval and the benefit of earlier diagnosis in terms of life-years (quality-adjusted life years (QALY)).

Until now, risk factors for a long total interval in adult sarcoma care as well as its effect on clinical and patient-reported outcomes remain unknown. These need to be studied in well-designed, large, prospective studies in order to prioritise interventions to optimise the total interval. Our study aims to quantify total interval, identify independent variables associated with a long interval (such as demographic and clinical factors) and determine the association between total interval and other dependent variables, such as HRQoL, stage and tumour size at diagnosis, progression-free survival (PFS) and OS (figure 1).

**Figure 1 F1:**
[figure not shown]
Conceptual model.

## Methods and analysis

### Study design and setting

We will conduct a longitudinal, prospective, cohort study among adult sarcoma patients, newly diagnosed in one of the participating study centres (five centres in the Netherlands: Radboud University Medical Centre Nijmegen, Erasmus Medical Centre Rotterdam, University Medical Centre Leiden, University Medical Centre Groningen, Netherlands Cancer Institute Amsterdam; three centres in the UK: The Royal Marsden London, Christie Manchester, Royal Orthopaedic Hospital Birmingham, all NHS Foundation Trusts). The study started recruitment at the first centre in the Netherlands in February 2018 and in the UK in October 2018 and is currently recruiting.

After informed consent, patients are being asked to complete questionnaires at five points in time: the first at baseline, preferably before start of treatment or within 4 weeks thereafter, and at 3, 6, 12 and 24 months follow-up (table 1). Baseline questionnaire completion will take about 45 min, follow-up questionnaires will take 20–30 min each.

**Table 1 T1:** Time points and questionnaire items

Item (number of items)	Scale	0 months	3 months	6 months	12 months	24 months
Characteristics						
Sociodemographic (max 20)		X	X	X	X	X
Comorbidity (15)	SCQ	X			X	X
Total interval (max 42)	Own design	X	X	X	X	X
Health literacy (1)	SBSQ	X				
Social support (1)	QLCS	X		X		X
Self-efficacy (10)	GSE	X				
Coping (28)	Brief COPE		X			
Resilience (6)	BRS			X		
Outcomes						
Health-related quality of life (30)	EORTC QLQ-C30 version 3.0	X	X	X	X	X
Quality-adjusted life years (6)	EQ5D5L	X	X	X	X	X
Psychological distress (14)	HADS	X	X	X	X	X
Financial impact (20)	Own design	X	X	X	X	X
Information provision (max 26)	Profiles registry		X			
Quality of care (max 23)	PSQ-18 and 3–5 single items	X	X	X	X	X
Total number of items		194	158	105	113	114

BRS, brief resilience scale; COPE, Coping Orientation to Problems Experienced; EORTC QLQ, European Organisation for Research and Treatment of Cancer Quality of Life Questionnaire; EQ5D5L, European Quality of life 5 Dimensions 5 Levels; GSE, general self-efficacy; HADS, hospital anxiety and depression scale; PSQ, patient satisfaction questionnaire; QLCS, quality of life-cancer survivors; SBSQ, set of brief screening questions; SCQ, self-administered comorbidity questionnaire.

### Patient and public involvement

The different patient-reported outcome measures were selected in consultation with patient advocates. The Sarcoma Patients EuroNet, an international network of patient advocacy groups, has formulated research priorities, at least two of which will be addressed by our study: (1) earlier diagnosis and (2) patient-reported outcomes such as HRQoL.^20^ The questionnaire was pilot tested by patients, for acceptability and understandability. Study documents were reviewed by the patients who are members of the Royal Marsden Hospital Patient and Public involvement panel, and the ethics committee of Radboudumc. The panel and committee provided feedback on the protocol, questionnaires, patient information sheet and informed consent form, regarding content and readability, and changes were incorporated in the final documents. Patients have been and will be involved in study-related presentations and publications.

### Participants

Eligible patients are invited by their treating physician or a member of the research team. Inclusion criteria are: (1) aged ≥18 years; (2) new histological diagnosis of sarcoma as confirmed by a sarcoma histopathologist (according to the International Statistical Classification Of Diseases And Related Health Problems, 10th revision, German Modification (ICD-10-GM) codes C40 and C41 for bone sarcoma and C49 for soft-tissue sarcoma); (3) able to communicate in English or Dutch and to complete questionnaires themselves; (4) mental capacity to provide informed consent and participate in the study (as determined by the healthcare professional) and (5) diagnosed at or referred to one of the participating hospitals. Exclusion criteria are: (1) too ill to complete questionnaires (according to treating physician—patients who experience symptoms are still eligible); (2) desmoid fibromatosis and gastrointestinal stromal tumours due to the different nature of the diseases (ICD-10-GM codes C15-20, C26, C48 and C80).

### Data collection

Eligible patients receive a patient information sheet, which explains the goals and procedure of the study. It includes a link to a secure website (www.profielstudie.nl for both English and Dutch patients), a login name and a password. After logging in, patients can provide informed consent and complete questionnaires online. Patients without access to internet or preference of written communication receive a paper version of the informed consent form and questionnaire. Questionnaires completed on paper will be entered via the data entry option into the Patient Reported Outcomes Following Initial treatment and Long term Evaluation of Survivorship system (PROFILES; www.profilesregistry.nl^21^) by a member of the study team. The data entry portal has the same format as the online questionnaire data, minimising the chance of errors and enhancing data extraction. Paper questionnaires will be stored in a secured room at study coordinating sites (Radboudumc and Royal Marsden Hospital). PROFILES is a data management system set up in 2009 in the Netherlands for the study of physical and psychosocial impact of cancer and its treatment. The data collected in PROFILES is stored on a secure server in the Netherlands. In order to retrieve the data, an authorised member of the study team can login and download an SPSS or Excel file containing the encoded questionnaire data. PROFILES has been developed to the requirements of the higher education and research community and allows end-to-end encryption.

The research coordinator has access to a password-protected file that links patients’ study numbers to their electronical patient record number. Clinical data and survival data will be retrieved from the patients’ medical record by a member of the study team into the electronic case report forms (eCRF) database (MACRO), which is maintained according to current norms and International Council for Harmonisation of Technical Requirements for Registration of Pharmaceuticals for Human Use - Good Clinical Practice (ICH-GCP)) standards and is password protected. Patient records will not leave the hospital.

Finally, questionnaire data will be linked with the eCRF database (all encoded data) using study numbers. The combined dataset will be stored under appropriate password protection. Data will be recorded and retained in accordance with the Data Protection Act 1998.

### Case report forms

CRFs will be completed at five time points during the study. The first will be completed on inclusion, the following time points coincide with the completion of follow-up questionnaires. The last CRF is also the end-of-study CRF, which can be completed before 24 months if a patient withdraws or deceases. The information collected on the CRF will be stored on a secure CRF database using anonymous study numbers. Data collected includes documentation of eligibility criteria, date of diagnosis, tumour characteristics such as histology, tumour, node and metastasis (TNM) stage, tumour size, treatment regiment, re-occurrence of disease or metastases, reason for withdrawal of the study and time of death, if applicable.

### Questionnaires

We have combined self-designed questions and several validated questionnaires designed by other researchers (details below). For non-commercial scientific use, no formal licenses are needed for the use of these questionnaires. Self-designed items and existent questionnaires not available in both English and Dutch were translated with formal forward-backward translation by bilingual speakers. Table 1 summarises the time points at which each construct is being measured.

### Sociodemographics

The questionnaires contain questions on sociodemographic characteristics of the participant at the time of questionnaire completion, such as marital status and educational level. Comorbidity is being measured with the Self-administered Comorbidity Questionnaire (SCQ), which is a validated list where patients report their comorbidity during the past year.^22^

### Total interval

A 42-item list was self-designed to assess the total interval. Examples of questions are as follows: ‘With which symptom(s), caused by the sarcoma, did you first go to a doctor?’, ‘To which doctor did you first talk about your symptoms?’ and ‘How often did you talk to the following doctors about your symptoms belonging to sarcoma, before you heard you had a sarcoma?’ At follow-up, a few questions are repeated to complete data collection. We will sample survey the reported dates by cross-checking them with the patient’s record. If more than 5% of the cross-checked dates deviates more than 1 month from the registered dates in the medical record, we will cross-check all dates and use the clinical reported dates for statistical analysis.

Health literacy is being assessed by a Dutch adaptation of Chew’s Set of Brief Screening Questions (SBSQ) in a single-item question.^23–25^

Social support is being assessed by one single item: ‘Was the amount of support you received from others sufficient?’ extracted from the Quality of Life-Cancer Survivors questionnaire.^26 27^

Self-efficacy is measured with the General Self-Efficacy scale (GSE).^28^ This 10-item scale assesses a general sense of perceived self-efficacy with the aim to predict coping with daily hassles as well as adaptation after experiencing a stressful life event. Self-efficacy is the belief that one can perform a novel or difficult task, or cope with adversity. Perceived self-efficacy facilitates goal-setting, effort investment, persistence in face of barriers and recovery from setbacks. Responses are made on a 4-point scale. A higher final composite score correlates with higher perceived self-efficacy.

Coping is assessed in the 3-month questionnaire with the help of the brief Coping Orientation to Problems Experienced (COPE).^29^ Coping is about emotional and mental reactions, which enable people to activate sources of help needed to cope with stress and problems. This 28-item scale measures 14 positive and negative styles of coping on a 5-point Likert-scale.

Resilience is measured in the 6-month questionnaire using the Brief Resilience Scale (BRS).^30^ Resilience is a skill that helps people recover from a life event. People with high (perceived) resilience can move on faster after a setback. The BRS is a 6-item scale with a 5-point Likert scale.

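### One pooled date check can switch every date to the medical record, including the first-symptom date, for which the record is not shown to be more accurate

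*Protocol article*

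**What the plan says.** The Introduction defines the study's central variable: "The time between first symptom and (histological) diagnosis is known as the total interval". Its first component, the patient interval, is "defined as time between onset of symptoms until consultation of a healthcare professional".

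Under Total interval, dates come from a self-designed questionnaire and are verified in two steps. First, "We will sample survey the reported dates by cross-checking them with the patient’s record". Second, the trigger: "If more than 5% of the cross-checked dates deviates more than 1 month from the registered dates in the medical record", then "we will cross-check all dates and use the clinical reported dates for statistical analysis". The article does not give the number of dates sampled, does not distinguish first symptom, first consultation, referral and diagnosis, and exempts none of them.

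Two other places bear on this. Case report forms describes what is extracted from the record: "Data collected includes documentation of eligibility criteria, date of diagnosis, tumour characteristics such as histology", and further items. Date of diagnosis is named and a first-symptom date is not, although the list is not presented as complete. The strengths and limitations list claims: "Inclusion of patients at diagnosis minimises recall bias for total interval length".

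**The concern.** The two ends of the total interval differ in kind. The diagnosis date is generated by the healthcare system, and the record is its source document. The onset date is generated by the patient before any clinician is involved, so what the record holds is the patient's account as noted later. When questionnaire and record disagree on onset, the disagreement does not show which is wrong. The rule nevertheless always decides for the record.

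The trigger is also a single percentage over all date types. Agreeing diagnosis dates can mask poor agreement on onset. Conversely, poor agreement on onset can change the source of dates that were in good order.

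At stake is the variable that all three aims rest on. Total interval is quantified, modelled as an outcome of risk factors, and then related to HRQoL, stage, tumour size, PFS and OS. It also supplies the cut-off, or the last quartile, that defines a long interval in the later analyses. A change of source for its starting date passes into all of these.

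**Working it through.** The article states no figure that depends on this rule, so there is nothing to reproduce. The check is a comparison of the text, followed by arithmetic on the trigger.

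**1. Text side by side**

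| Date | Where it arises, per the article | Status of a record entry |
|---|---|---|
| First symptom | Start of the patient interval, before any consultation (Introduction) | Later note of the patient's account |
| First consultation | In general with a GP (Introduction); clinical data are taken from the patient's record, and "Patient records will not leave the hospital" (Data collection) | May be second-hand at the participating hospital |
| Referral, hospital visits | Within the healthcare system | Contemporaneous where documented |
| Histological diagnosis | Healthcare system; named among the case report form data | Source document |

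The rule under Total interval applies one criterion and one consequence to all four rows.

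**2. What the pooled 5% means for onset**

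Let *w* be the share of checked dates that are first-symptom dates, *d* the proportion of those off by more than 1 month, and *o* the same proportion for all other dates. The pooled rate is *w·d* + (1 − *w*)·*o*. Setting it to 0.05 gives *d* = (0.05 − (1 − *w*)·*o*) / *w*. The article gives neither *w* nor *o*; the values below are assumptions.

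| *w* | *o* = 0 | *o* = 0.01 | *o* = 0.02 |
|---|---|---|---|
| 1/2 | 0.05/0.50 = 10% | 9% | 8% |
| 1/3 | 0.05/0.333 = 15% | 13% | 11% |
| 1/4 | 0.05/0.25 = 20% | 17% | 14% |

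The column *o* = 0 shows both faults. Up to these values, onset disagreement two to four times the nominal 5% passes unnoticed. Beyond them, onset dates alone trip the rule and replace every date, although all the others agree.

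**3. Chance that the trigger fires (illustration only)**

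For *m* dates checked and a true pooled deviation rate *p*, the rule fires if X > 0.05*m* with X ~ Binomial(*m*, *p*). For an assumed *m* = 150, that is X ≥ 8:

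| *p* | 2% | 3% | 4% | 5% | 8% | 10% |
|---|---|---|---|---|---|---|
| P(fires) | 0.01 | 0.08 | 0.25 | 0.48 | 0.92 | 0.99 |

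The assumed sample size also matters. At *p* = 5% the probability is 0.26 for 20 dates, 0.46 for 50, 0.38 for 100 and 0.42 for 200; at *p* = 10% it is 0.61, 0.89, 0.94 and 0.99. With neither *m* nor *p* in the article, the result runs from almost never to almost always.

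**The case against.** Four arguments stand against the point.

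- **The record may be better, even for onset.** A history taken at referral or first visit may predate the baseline questionnaire, which can be completed up to 4 weeks after the start of treatment. Such a note could carry less recall error. This stands. The article does not compare the two sources, so it supports only that the record is not shown to be better for onset, not that it is worse.
- **Only registered dates can be compared.** The trigger refers to dates registered in the record, so an onset date with no record counterpart may fall outside the rule. This narrower reading is possible, though the text does not state it. It answers an inference a reader might draw, that patients whose records lack an onset date would lose their interval. The article does not say that patient dates are discarded with nothing to replace them, and it gives no rate of missing record dates. A count of patients lost would be guesswork. The narrower reading does leave an onset variable of mixed source.
- **Dilution makes replacement less likely.** True: masking and over-replacement cannot happen in the same check. They are two failure modes of one pooled criterion, and which one occurs depends on the mix of dates sampled.
- **This is operational detail that an article may leave to a fuller document.** That holds for the size of the sample and the handling of absent dates. It does not hold for the replacement rule, which the article itself states, without exception by date type.

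**Conclusion.** The point holds as a defect in a stated rule. A single pooled check decides the source of all dates, although the record is the source document for diagnosis and only a later account for first symptom. The conclusion rests on the article's own definition of the interval and on the plain wording of the rule.

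Its size can be given only conditionally. With onset dates making up one half to one quarter of those checked and all others agreeing, onset disagreement of 10% to 20% merely reaches the threshold.

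A reader might infer that the trigger is likely to fire. The article does not support that: it gives neither the number of dates checked nor a deviation rate, and for an assumed 150 dates the probability goes from 0.01 at a true 2% to 0.99 at 10%. A reader might also infer bias in the Dutch-English comparison. That would require record completeness to differ by country, on which the article gives no information.

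**What to change.** Reword the rule under Total interval so that the source is set by date type:

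- **Histological diagnosis:** take the date from the case report form for every patient, whatever the check shows.
- **Referral and hospital visits:** use the record where the date is documented there.
- **First symptom:** keep the baseline patient-reported date as the primary source for all patients, with no automatic overwriting. Repeat the main analyses with the record-based onset date, where present, as a sensitivity analysis.
- **Check:** apply the 5% / 1-month criterion separately to each date type and report agreement by type.

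The cost is a change of wording, best made before analysis. The diagnosis date is already collected, and neither sample size nor questionnaires change. The sensitivity analysis uses onset dates that are in the record anyway, though they have to be abstracted where present. The downside is that recall error in the patient-reported onset date remains and must be acknowledged as a limitation.
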